The stratification used for randomisation will ensure balance in treatment allocation across recruitment centres. In addition to the unadjusted analyses, we will also undertake regression analyses to adjust for any imbalance between treatment groups in patient baseline (preinjury) EQ-5D, age and gender. Age and gender are likely to be reported by all study participants, however, if baseline EQ-5D is poorly reported, such that it reduces the available sample size for the definitive analysis, then it will not be included in the definitive model. The fixed-effects analysis (linear regression model) will be generalised by adding a random effect for recruitment centre to allow for possible heterogeneity in patient outcomes due more generally to the recruitment centre. The adjusted mixed-effects regression will be the definitive (primary) analyses and will be reported as such. Analyses will be undertaken using the specialist mixed-effects modelling functions available in the software package R (http://www.r-project.org/).^17^ EQ-5D data will be assumed to be approximately normally distributed; possibly after appropriate variance-stabilising transformation. The primary focus will be the comparison of the two treatment groups of patients, and this will be reflected in the analysis which will be reported together with appropriate diagnostic plots that check the underlying model assumptions. Results will be presented as mean differences between the trial groups, with 95% CIs. The primary analysis will be on an ITT basis. However, a per-protocol analysis will also be undertaken by repeating the primary outcome analysis using the actual treatment received by participants (in contrast to the allocated treatment) as a sensitivity analysis to examine the robustness of conclusions to different assumptions about departures from the stated protocol.

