In addition to the cross-sectional analysis at 4 months, we will also perform a longitudinal analysis of EQ-5D data collected at all study time points (1, 4 and 12 months) to a single value, namely the area under the curve (AUC) and facilitated comparisons of the AUCs between treatment groups. It is advisable in the presence of missing data to use summary statistics generated by mixed models, as estimates will not be biassed under the assumption that data are missing at random, or completely at random. Therefore, we will fit a repeated measures mixed model, with the same fixed effect structure as used in the primary analyses, but with a three level random effects structure where observations (time points) are nested within participants, and participants nested within recruitment centre.

It seems likely that some data may not be available due to voluntary withdrawal of patients, lack of completion of individual data items or general lost to follow-up. Where possible the reasons for data ‘missingness’ will be ascertained and reported. Although missing data are not expected to be a problem for this study, the nature and pattern of the missingness will be carefully considered—including in particular whether data can be treated as missing at random (MAR). If judged appropriate, missing data will be imputed using the multiple imputation facilities available in R.^18^ Any imputation methods used for scores and other derived variables will be carefully considered and justified. If the degree of missingness is relatively low, as expected, the primary analysis will be based on complete cases only (complete-case analysis), with analysis of imputed datasets used to assess the sensitivity of the analysis to the missing data. Reasons for ineligibility, non-compliance, withdrawal or other protocol violations will be stated and any patterns summarised. More formal analysis, for example, using logistic regression with ‘protocol violation’ as a response, may also be appropriate and aid interpretation.

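### As written, the mixed model behind the EQ-5D area under the curve has no visit or treatment-by-visit term, so its AUC difference is reliable only if the treatment effect is constant over time and missingness does not differ by arm

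*Protocol article*

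**What the plan says.** All of this is in the Statistical analysis section of the Protocol article.

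- **Primary model.** Regression of 4-month EQ-5D on treatment, extended to "adjust for any imbalance between treatment groups in patient baseline (preinjury) EQ-5D, age and gender". Baseline EQ-5D is dropped if poor reporting would reduce the sample. The model is completed by "adding a random effect for recruitment centre to allow for possible heterogeneity in patient outcomes".
- **Longitudinal analysis.** This is introduced with "In addition to the cross-sectional analysis at 4 months". It reduces EQ-5D at 1, 4 and 12 months to one number, "namely the area under the curve (AUC) and facilitated comparisons of the AUCs between treatment groups".
- **Model for it.** The plan states "we will fit a repeated measures mixed model, with the same fixed effect structure as used in the primary analyses". The one contrast drawn with the primary model is a "three level random effects structure where observations (time points) are nested within participants", with participants in turn nested within centre.
- **Reason for a mixed model.** The plan says "estimates will not be biassed under the assumption that data are missing at random, or completely at random".

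**The concern.** An area under the curve is a weighted sum of visit means, so comparing AUCs between arms needs a treatment effect at each visit. A model built for one time point cannot contain a time term. If its fixed effects are carried over unchanged, time enters the longitudinal model only as a nesting level. The fitted mean is then flat from 1 to 12 months and the treatment effect is forced to be the same at every visit.

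Two things are at stake. If the effect fades or grows during recovery, the reported AUC difference is generally wrong. And if the arms differ in who responds at which visit, the recovery trend itself can appear as a treatment effect, which undercuts the reason given for choosing a mixed model.

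**Working it through.** The plan gives no figure for this analysis, so there is none to reproduce. The check compares what the stated model delivers with what an AUC requires.

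**Inputs from the plan.** Visits at 1, 4 and 12 months; fixed effects as in the primary model; minimal important difference 0.075 and target of 1128 participants (Sample size). **Assumed here.** The trapezoid rule, the effect patterns, visit means, variances and response rates; none of these is in the article.

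**Step 1: weights.** The intervals are 3 and 8 months. With visit-specific effects d1, d4 and d12, the trapezoid gives

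3(d1 + d4)/2 + 8(d4 + d12)/2 = 1.5·d1 + 5.5·d4 + 4·d12.

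The weights sum to 11 months; as proportions they are 0.136, 0.500 and 0.364.

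**Step 2: the model as written.** It has one treatment coefficient b, so its AUC difference is 11·b. With complete data b is the simple mean of the three visit effects, a weight of 1/3 each.

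**Step 3: complete-data comparison (utility-months).**

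| Assumed effect at 1 / 4 / 12 months | Trapezoid | As written | Error |
|---|---|---|---|
| 0.075 / 0.075 / 0.075 | 0.825 | 0.825 | none |
| 0.10 / 0.05 / 0 | 0.425 | 0.550 | +29% |
| 0 / 0.05 / 0.10 | 0.675 | 0.550 | −19% |
| 0 / 0.075 / 0 | 0.4125 | 0.275 | −33% |
| −0.075 / 0 / 0.075 | 0.1875 | 0 | all lost |

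Second row: 1.5 × 0.10 + 5.5 × 0.05 + 4 × 0 = 0.425, against 11 × (0.10 + 0.05 + 0)/3 = 0.55. The gap of 0.125 utility-months is 0.125/11 = 0.011 on the EQ-5D scale averaged over the period, about 15% of 0.075.

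**Step 4: incomplete data.** A simulation used 1128 participants, 60 replicates, visit means of 0.35, 0.45 and 0.50, and a random participant intercept. Centre and covariates were left out. Missingness depended only on visit and, in the last row, arm. Response was 75/60/50% in both arms, except in the last row (75/60/50% against 60/60/60%). Monte Carlo standard errors were 0.023 to 0.029.

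| Scenario | True | As written | With visit and treatment-by-visit |
|---|---|---|---|
| Constant 0.075 | 0.825 | 0.861 | 0.867 |
| Fading 0.10 / 0.05 / 0 | 0.425 | 0.660 | 0.446 |
| Growing 0 / 0.05 / 0.10 | 0.675 | 0.431 | 0.645 |
| Crossing −0.075 / 0 / 0.075 | 0.188 | −0.147 | 0.184 |
| No effect, equal response | 0 | 0.007 | −0.002 |
| No effect, response differing by arm and visit | 0 | 0.174 | 0.043 |

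Falling response moves weight towards the early visits, which enlarges the error; in the crossing case the sign is wrong. In the last row the model as written is 0.174/0.023 = 7.6 standard errors from zero. The model with visit terms is 0.043/0.024 = 1.8 from zero, which is compatible with no bias. On the EQ-5D scale 0.174/11 = 0.016.

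**Step 5: does the missing-at-random argument hold?** It requires a correct model for the mean. In the last row missingness depends on arm and visit alone. The model as written conditions on arm but not on visit, so with a rising mean the protection is lost.

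**The case against.** The best reply is that the sentence means the same covariate adjustment, with time understood in a repeated-measures model, since without a time term there is no curve to summarise. The exact formula of a supplementary model is also something an article leaves to its analysis plan. The authors may well have intended this. But the article is not silent: it fixes the fixed part by reference to a single-time-point model and names only the random part as different. A statistician following it would fit the model examined here.

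Other parts of the reply stand and limit the point.

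- A reader might infer that the model cannot estimate the AUC difference at all. It can: with a constant effect and missingness that does not differ by arm, 11 times the coefficient is the right quantity.
- A reader might infer that the unbiasedness claim is simply false. The spurious effect in the simulation needed both a mean that changes over time and missingness that differs by arm and visit. With equal response and no effect there was no bias.
- A reader might infer that a changing effect would go unseen. EQ-5D at 1 and 12 months are secondary outcomes analysed by the primary strategy, so together with the 4-month analysis all three visit-specific effects will be reported. The AUC is not itself listed among the objectives or outcome measures.
- Every magnitude above rests on assumed patterns, and the steep trends were chosen to illustrate.

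Against the last item, the conditions are not remote. The Sample size section expects only 60% of participants to be available at 4 months. Deaths are scored as zero in all analyses, so accumulating deaths alone can shift the visit means.

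**Conclusion.** The point holds as a defect in how a supplementary analysis is specified. Taken as written, the model has no visit or treatment-by-visit term and delivers 11 months times one coefficient. That is correct for a constant effect with missingness not differing by arm, and in general wrong when the effect varies over time. Under the assumed monotone patterns the complete-data error is +29% or −19%; no single figure can be given for this trial, because the article supplies neither effect patterns nor response rates by arm and visit.

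The conclusion does not depend on which covariate list is meant. The abstract names age, gender and cognitive impairment, and the Statistical analysis section names baseline EQ-5D (conditionally), age and gender; neither includes time. Nothing here bears on the 4-month primary analysis or on the target of 1128.

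**What to change.** In the Statistical analysis section, state that the repeated-measures model adds categorical visit (1, 4 and 12 months) and treatment-by-visit to the primary model's fixed effects, keeping the participant and centre random effects. State that the between-group AUC difference is the contrast 1.5·d1 + 5.5·d4 + 4·d12 of the visit-specific treatment effects, reported with its 95% CI. Baseline-by-visit (only if baseline EQ-5D is retained) and an unstructured within-participant covariance are optional refinements.

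The cost is one or two sentences and no extra data. The price is a few more parameters and a slightly wider interval: across the six simulated scenarios the ratio of Monte Carlo standard errors, with and without the visit terms, ran from 1.00 to 0.028/0.026 = 1.08, a rough guide given 60 replicates and rounding.

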### Sample size

The best available evidence we have from data collected during previously performed studies in this patient population suggests that the SD for EQ-5D-5L at 4 months postinjury is approximately 0.3 points.^10^ The best available evidence for what constitutes a minimal important difference (MID) for EQ-5D comes from a review of MID estimates.^14^ A review of the literature shows an estimated median value of 0.08 for the MID for EQ-5D. Using our previously established standard deviation (SD=0.33), this suggests a standardised effect size of approximately 0.24; a ‘small to moderate effect’ based on Cohen’s criteria.^15^ Assuming that the EQ-5D at 4 months postinjury has an approximate normal distribution, which Parsons *et al*
10 suggest is reasonable, and a 1:1 allocation ratio, then if the true difference between the experimental and control group EQ-5D means is in the range 0.07–0.08, we will need to recruit the below number of participants (see table 1) in each group to be able to reject the null hypothesis that the population means are equal with probability (power) 0.8 and 0.9 and type I error rate of 5% (significance).

**Table 1 T1:** Group sizes required following sample size calculations

Power, %	MCID		
	**0.07**	**0.075**	**0.08**
80	290	253	222
90	387	338	297

MCID, minimal clinically important difference.

Taking the intermediate minimal clinically important difference of 0.075, for 80% (90%) power, we would need to recruit 253 (338) patients in both the experimental arm and in the control arm, 506 (676) in total. In this population we expect considerable lost to follow-up due mainly to patients declining consent to further follow-up and incapacity, so we have assumed that only 60% of recruited study participants will be available at the definitive endpoint at 4 months. This gives a total sample size of 844 for 80% power and 1128 for 90% power. Conservatively, we aim to recruit 1128 to ensure 90% power based on these assumptions.

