### Statistical analysis

The main analysis will investigate differences in the primary outcome measure, EQ-5D (HRQoL), between the two treatment groups on an intention-to-treat (ITT) basis at 4 months postinjury on a complete-case basis. The ‘death-adjusted’ ED-5D measure, imputing death as zero, is the preferred analysis option in this population, and will be used for all analyses.^16^ An initial analysis will test for differences between treatment groups using linear regression analysis, based on a Normal approximation for EQ-5D. Tests will be two sided and considered to provide evidence for a significant difference if p values are less than 0.05 (5% significance level). Estimates of treatment effects will be presented with 95% CIs.

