### Economic analysis

A within-trial cost-effectiveness analysis of cemented versus uncemented hemiarthroplasty in participants over 60 years of age with a displaced intracapsular hip fracture will be conducted from the UK NHS and Personal Social Services perspective^19^ in the base case analysis. Resource utilisation involving differences in surgical treatments between the two intervention groups will be obtained from case report forms (CRFs) that would be completed by the local research teams. Broader resource utilisation will be captured through CRFs and patient questionnaires administered at baseline, 1 month, 4 months and 12 months postinjury. Unit costs for health and social care resources will largely be derived from the latest available local and national sources and estimated in line with best practice. Costs will be standardised to current prices where appropriate. An incremental cost-effectiveness analysis, expressed in terms of incremental cost per quality-adjusted life year gained, will be performed. Results will be presented using incremental cost-effectiveness ratios (ICERs), net monetary benefit and cost-effectiveness acceptability curves generated via non-parametric bootstrapping. Multiple imputation methods will be used to impute missing data and avoid biases associated with complete-case analysis. Sensitivity analyses involving economic analysis from the societal perspective and extending the time frame from 4 months to 1 year will also be conducted.

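### The complete-case primary analysis is made conditional on low missingness, while the sample size assumes that 40% of 4-month outcomes will be missing

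*Protocol article*

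**What the plan says.** Two sections of the protocol article forecast the same quantity differently.

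- **Sample size.** The authors expect substantial loss, mainly because patients refuse further follow-up or lack capacity, "so we have assumed that only 60% of recruited study participants will be available at the definitive endpoint at 4 months". The target follows from this: "Conservatively, we aim to recruit 1128 to ensure 90% power based on these assumptions".
- **Statistical analysis, missing-data paragraph.** It includes the clause "Although missing data are not expected to be a problem for this study". The primary analysis is complete-case provided that missingness turns out fairly low, which the text says is expected. In that case imputation has a supporting role, "with analysis of imputed datasets used to assess the sensitivity of the analysis to the missing data". Imputation is itself subject to a judgement of appropriateness. Missing at random (MAR) is the only mechanism raised in connection with imputation.
- **Statistical analysis, opening paragraph.** The main 4-month comparison is set as complete-case with no condition attached. Deaths are scored zero.
- **Statistical analysis, longitudinal paragraph.** A repeated-measures mixed model over 1, 4 and 12 months supports an area-under-the-curve (AUC) comparison. It is justified under MAR or missing completely at random.
- **Economic analysis.** Imputation is planned without condition: "Multiple imputation methods will be used to impute missing data and avoid biases associated with complete-case analysis".

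**The concern.** A forecast of 40% loss and a forecast of low loss cannot both be the plan. The conflict matters because the second forecast is the stated condition for the primary analysis. If loss is near 40%, the condition is not met and the text does not say what the primary analysis becomes. It gives no threshold for low missingness and makes imputation discretionary, while the opening paragraph prescribes complete cases regardless. Whoever analyses the trial could therefore defend more than one primary analysis after seeing the data.

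The proportion missing also determines how much the choice matters. At 5% or 10% missing, almost any reasonable handling gives the same answer. At 40%, a moderate difference between arms in how the unobserved compare with the observed can change the conclusion. Incapacity, named as a main cause of loss, may well be related to the quality-of-life score that goes unrecorded.

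**Working it through.** **Inputs**
- Difference: "Taking the intermediate minimal clinically important difference of 0.075" (Sample size).
- Error rate and sidedness: 5% (Sample size); "Tests will be two sided and considered to provide evidence for a significant difference if p values are less than 0.05" (Statistical analysis).
- Power 90%, 1:1 allocation, 60% available at 4 months (Sample size).
- SD 0.30. The Sample size section gives both about 0.3 and 0.33. All six cells of Table 1 reproduce with 0.30. With 0.33 the cell used would be 408 per arm, not 338.

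**1. Reproduce the plan's figure.** The two-sample t-test with difference 0.075 and SD 0.30 needs 338 per arm, or 676 in total. Allowing for 60% availability, 676 / 0.6 = 1126.7, which rounds up to 1127. Rounding by arm, 338 / 0.6 = 563.3, so 564 per arm and 1128 in total. The target reproduces, and only with 40% loss.

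**2. What 40% means.** 0.40 × 1128 = 451 participants without a primary outcome, and 0.60 × 1128 = 677 analysed.

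**3. What low missingness would imply.** At 5% loss, 676 / 0.95 gives 712 recruits; at 10%, 676 / 0.90 gives 752. With 1128 recruited and 5% or 10% loss, power would be about 98%. The recruitment target therefore contradicts the low-missingness premise.

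**4. Could deaths explain the gap?** No. A death is scored zero and so has an outcome. The Sample size section attributes the loss mainly to refusal of follow-up and incapacity.

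**5. Precision.** SE = 0.30 × √(2/338) = 0.0231. Critical difference = 1.9635 × 0.0231 = 0.0453.

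**6. Tipping point.** Let a proportion m be missing in each arm, and let the between-arm difference among the unobserved be smaller than among the observed by d. The all-randomised difference is then the observed difference minus m × d. Keeping the SE at 0.0231, an observed 0.075 falls to the critical difference when d = (0.075 − 0.0453) / m.

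| m | d, 338 observed per arm | d, 1128 recruited |
|---|---|---|
| 30% | 0.099 | 0.110 |
| 40% | 0.074 | 0.074 |
| 50% | 0.059 | 0.051 |

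At 40%, the difference among the unobserved would be 0.075 − 0.074, or about zero.

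**7. Size of a possible bias.** With equal loss in both arms, complete-case bias = m × g, where g is the between-arm difference in the gap (observed mean minus missing mean). The documents do not give g, so its range is assumed. At m = 0.40, g of 0.05, 0.10, 0.15 or 0.20 gives a bias of 0.02, 0.04, 0.06 or 0.08. A bias as large as the whole 0.075 needs g = 0.075 / 0.40 = 0.1875. At 10% or 5% missing it would need 0.75 or 1.5.

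**8. Type I error.** Suppose the all-randomised difference is zero and the complete-case estimate carries bias b. The two-sided rejection rate is 1 − Φ(1.96 − b/SE) + Φ(−1.96 − b/SE). For b = 0.02, 0.03 and 0.04 this gives 13.9%, 25.5% and 41.0%.

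**9. What MAR imputation can and cannot do.** When only the 4-month outcome is missing and the imputation uses just the primary model's covariates, the incomplete records add no information, and the result essentially repeats the complete-case regression. With further variables it need not. An illustrative simulation used 564 per arm, no true effect, about 40% missing, and missingness related to outcome in one arm only. All of its parameters are assumed, and imputation was by regression on a baseline covariate and the 1-month score.
- Missingness driven by the 1-month score: complete-case bias 0.057; about 0.00 after imputation.
- Missingness driven by the unseen 4-month score: complete-case bias 0.10; 0.065 remains after imputation.

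**The case against.** Several points on the other side stand.

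- A reader might infer that the imputation check is empty and can only agree with the primary result. The documents do not support that. They do not specify the imputation model and promise that its methods will be considered and justified. The 1-month score is collected, and step 9 shows that imputation using it can expose bias which that score explains.
- Imputation is not the only approach named. The repeated-measures model uses participants with partial follow-up. It targets the AUC and also relies on MAR, so it too leaves open missingness that depends on the unseen 4-month score.
- The design limits the risk. Deaths are scored zero. The Primary outcome measure section cites support for proxy reporting in cognitive impairment. Participants are blinded, which makes non-response that differs by arm less likely. Under equal loss, bias in the treatment contrast needs an arm-specific gap, and dependence on outcome alone does not establish one.
- A reader might take the Economic analysis section as rejecting complete cases for the primary outcome. It concerns costs and quality-adjusted life years over several time points and does not pronounce on the 4-month regression.
- An analysis allowing data to be missing not at random is commonly left to the SAP, which is not shown. Its absence here is not a defect.

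None of this reconciles the two forecasts or supplies the missing alternative to a complete-case analysis. The opening paragraph could be read as fixing complete cases outright, but the later paragraph then attaches a condition to the same choice.

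**Conclusion.** The Statistical analysis section states a premise that the Sample size section contradicts. On the trial's own forecast, the condition for the complete-case primary analysis is not met and nothing is put in its place. This follows from the text and from the arithmetic behind 1128, whatever the SAP adds.

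The numerical consequences are illustrations. They assume SD 0.30, 338 observed per arm and equal loss in both arms. The tipping value of about 0.074 and the type I error rates describe what 40% missingness could allow. The documents give no size for any bias and do not show that the complete-case estimate is biased. The point should be fixed before analysis; it does not show that the trial's result would be invalid.

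**What to change.** In the Statistical analysis section of the protocol, or in an SAP that expressly supersedes it:

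1. Replace the statements that missing data will be unproblematic and low with the 40% loss planned in the Sample size section.
2. Name one primary analysis that applies whatever degree of missingness is observed, and make the opening and missing-data paragraphs agree on it.
3. Run multiple imputation unconditionally, with auxiliary variables already collected: EQ-5D at 1 and 12 months, and cognitive status. The abstract lists cognitive status as an adjustment variable, but the definitive model in the Statistical analysis section does not include it.
4. If the SAP does not already contain one, add a delta-adjusted sensitivity analysis with separate shifts by arm, and report the shift at which the primary conclusion changes.

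The cost is some rewording and modest extra programming and reporting. No further patients or data are needed.

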Secondary analyses will be undertaken using the strategy described for the primary outcome for other approximately normally distributed outcome measures; for example, EQ-5D at 12 months. For dichotomous outcome variables, such as indicators of adverse events and other complications related to the trial interventions, mixed-effects logistic regression analysis will be undertaken with results presented as odds ratios (and 95% CIs) between the trial groups. The temporal patterns of any complications will be presented graphically and if appropriate a time-to-event analysis (Kaplan-Meier survival analysis) will be used to assess the overall risk and risk within individual classes of complications (eg, revision) and death. Cox’s proportional hazards regression will be used to test for differences in death rates between the trial intervention groups, after adjusting for age and gender. Multiple complications will be defined as two or more independent events, that is, not continuations of a previous complication, for the same patient and will be identified only after discussion with the clinical team.

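### Kaplan-Meier, named for the risk of revision and other non-fatal complications, censors deaths and so overstates the actual 12-month risk in the descriptive curves

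*Protocol article*

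**What the plan says.** All references are to the protocol article.

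- **Statistical analysis, last paragraph.** Complications are to be shown graphically over time. A further step is planned on condition that it is judged suitable: "time-to-event analysis (Kaplan-Meier survival analysis) will be used to assess the overall risk and risk within individual classes of complications (eg, revision". The same sentence goes on to include death. No competing-risk method is named, and nothing is said about how a death enters the curve for a non-fatal complication.
- **Same paragraph.** Dichotomous outcomes, including complications, are compared between groups by mixed-effects logistic regression and reported as odds ratios. For mortality a Cox model is planned: "proportional hazards regression will be used to test for differences in death rates between the trial intervention groups, after adjusting for age and gender".
- **Secondary objectives.** The quantity of interest is the proportion of participants with complications, including further surgery, in the first 12 months after injury. Mortality is a separate objective at 1, 4 and 12 months.
- **Statistical analysis, first paragraph.** For EQ-5D, death is scored as zero, so it counts as an outcome and not as missing data.

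**The concern.** A participant who dies unrevised can no longer be revised. Kaplan-Meier applied to time to revision has no place for that event: the participant leaves the risk set as censored, as if revision could still happen later. One minus Kaplan-Meier therefore gives the revision risk with death taken away, whereas the secondary objective asks for the proportion who have the complication. The two differ whenever deaths occur before 12 months, and Kaplan-Meier is always the higher.

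The cohort is aged 60 and over with hip fracture, and the authors expect enough deaths to build them into the EQ-5D score. Treating death as an outcome there and as ordinary censoring here is inconsistent. At stake are the absolute 12-month risks of revision and other complications that clinicians would read off the curves.

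**Working it through.** **Plan's own figure.** There is none to reproduce. The article states no mortality rate, revision rate or event count, and its sample size concerns EQ-5D only. The rates below are assumptions, chosen to show a range.

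**Assumed inputs.**
- Kaplan-Meier 12-month revision risk R = 5%, so the cumulative revision hazard is −ln(0.95) = 0.0513.
- Cumulative mortality at 1, 4 and 12 months: A = 5, 12, 20%; B = 7, 15, 25%; C = 8, 18, 30%.
- Revision timing: either a constant hazard over 12 months, or front-loaded with 40%, 35% and 25% of the hazard in months 0–1, 1–4 and 4–12.

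**Formula.** In interval k, let a be the cumulative revision hazard, b the cumulative death hazard, and S the proportion alive and unrevised at its start. The cumulative incidence gains S × a/(a+b) × (1 − exp(−(a+b))), and S is then multiplied by exp(−(a+b)). One minus Kaplan-Meier uses only the revision hazard and stays at 5% throughout.

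**Example: mortality A, constant revision hazard.**

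| Months | b | a | S at start | Gain |
|---|---|---|---|---|
| 0–1 | −ln(0.95) = 0.0513 | 0.0513 × 1/12 = 0.0043 | 1.000 | 0.42% |
| 1–4 | −ln(0.88/0.95) = 0.0765 | 0.0513 × 3/12 = 0.0128 | 0.946 | 1.16% |
| 4–12 | −ln(0.80/0.88) = 0.0953 | 0.0513 × 8/12 = 0.0342 | 0.865 | 2.78% |

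The gains sum to 4.35% (the rounded entries add to 4.36%). The ratio is 5.00/4.35 = 1.15 and the difference 0.65 points.

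**All cases, with a Kaplan-Meier risk of 5%.**

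| 12-month mortality | Revision timing | Cumulative incidence | Relative excess | Points |
|---|---|---|---|---|
| 20% (A) | constant | 4.35% | 15% | 0.65 |
| 25% (B) | constant | 4.18% | 20% | 0.82 |
| 30% (C) | constant | 4.02% | 24% | 0.98 |
| 20% (A) | front-loaded | 4.60% | 9% | 0.40 |
| 25% (B) | front-loaded | 4.49% | 11% | 0.51 |
| 30% (C) | front-loaded | 4.39% | 14% | 0.61 |

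**Check with both hazards constant.** Here the cumulative incidence is lr/(lr+ld) × (1 − exp(−(lr+ld))), with lr = −ln(1−R) and ld = −ln(1−D), where D is 12-month mortality. At D = 20, 25 and 30% it gives 4.49, 4.35 and 4.21%, an excess of 11, 15 and 19%, inside the range above. At D = 10% the excess is about 5%.

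**The case against.** The strongest case against has three parts.

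1. *The analysis is conditional and descriptive.* It is to be done only if appropriate, alongside graphs of when complications occur, and Kaplan-Meier is correct for death. That stands, and it limits the importance of the point. But if the analysis is run, the method named for classes such as revision is the wrong one for a risk.
2. *The article never says that deaths are censored.* True; it is inferred from the method. It is nevertheless what a standard Kaplan-Meier analysis of a non-fatal event does, and no composite with death is defined for these classes.
3. *The comparison of complications is by logistic regression.* True. If each participant is classed as having had the event or not, a death without revision counts as no event, and Kaplan-Meier censoring does not enter.

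Three stronger readings are tempting, but the article does not support them.

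- *A reader might infer that unequal mortality distorts the Kaplan-Meier comparison of the implants.* The Kaplan-Meier curve depends only on the revision hazard. With equal revision hazards it shows 5% in both arms, whatever the mortality. It is the cumulative incidence that moves: 4.35% against 4.02% if mortality were 20% and 30% under a constant revision hazard. A real contrast is enlarged on the absolute scale (3% v 5% by Kaplan-Meier is about 1.7 points in cumulative incidence at 25% mortality in both arms, both hazards constant), but no difference is created where there is none.
- *A reader might infer that costs are inflated.* The Economic analysis section takes resource use from case report forms and questionnaires, and no Kaplan-Meier estimate is said to feed it.
- *A reader might infer that the Cox model for death ignores centre, although "The stratification used for randomisation will ensure balance in treatment allocation across recruitment centres".* The Cox sentence names age and gender and is silent on centre. In a condensed article that is a detail which the analysis plan may supply, and leaving centre out would not make the test invalid.

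**Conclusion.** The point holds in limited form. Using Kaplan-Meier for the risk of revision and other non-fatal complications would overstate the actual 12-month risk. For assumed 12-month mortality of 20% to 30%, the relative excess is about 9% to 24%, or about 0.4 to 1.0 percentage points at a 5% Kaplan-Meier risk. The direction is certain; the size depends on mortality and on the timing of revisions, neither of which the article gives. The upper end needs front-loaded deaths with a constant revision hazard; if revisions also occur early, the excess is 9% to 14%. The effect is confined to descriptive absolute-risk curves and estimates. Neither the logistic comparison of complications nor the primary analysis changes.

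**What to change.** In the last paragraph of the Statistical analysis section, replace Kaplan-Meier with Aalen-Johansen cumulative incidence, with death as a competing event, for revision and the other non-fatal complication classes. Keep Kaplan-Meier for death and for any composite that includes death. If a time-to-event treatment effect on complications is reported, give cause-specific hazard ratios alongside the cumulative incidence, because the cumulative incidence of revision also depends on mortality.

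The cost is a wording change and slightly more analysis work. Deaths, revisions and complications are already to be taken from the medical record, so no new data are needed.
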